### Efficacy Outcomes

A total of 9 outcome measures will be used to test preliminary evidence of training efficacy. Specifically, 7 self-assessed outcome measures (ie, 5 questionnaires for parents and 2 questionnaires for adolescents), 2 performance-based tasks assessing social cognition taken from a standardized neuropsychological battery, and a virtual reality–based assessment of everyday setting EF will be used. Questionnaires will be sent to patients and families in a sealed envelope; after completing them, participants will be required to return them to the research staff using an envelope with a postmark included in the sealed envelope within 2 weeks. The performance-based subtests assessing social cognition and the virtual reality–based assessment will be administered remotely using the Google Meet videoconference platform.

A detailed description of outcome measures is provided in Textbox 4. The sample of this study will include adolescents aged 11 to 19 years, but some measures and questionnaires have been standardized for populations having a lower maximum age range; however, they will be adopted for this study as no other measures with the same characteristics are available in the Italian language. The individual measures affected by this problem are clearly described in Textbox 4.

All outcome measures will be administered at T0 (ie, preintervention assessment), T1 (ie, immediately after the 6-month intervention), and T2 (ie, 6 months after the end of the intervention).

For the questionnaire outcomes, approaches to missing individual items will follow the guidelines for missing item procedures indicated in the manual for each questionnaire. If no guidelines for individual missing items are available, the mean of the completed items will be used to replace missing items if ≤10% are missing.

A summary of outcome measures to test training efficacy is presented in Textbox 5.

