Description of outcome measures.Behavior Rating Inventory of Executive Function Second Edition (BRIEF-2)−parent form [64]: the BRIEF-2–parent form questionnaire is aimed at assessing executive functioning (EF) behaviors of children and adolescents (aged 5-18 years) in everyday life by considering their parents’ perspectives. The questionnaire is composed of 63 items referred to 9 different clinical scales (ie, inhibit, self-monitor, shift, emotional control, initiate, working memory, plan or organize, task-monitor, and organization of materials) and 3 validity scales (ie, inconsistency, negativity, and infrequency). BRIEF 2–parent form is administered to parents, who rate the frequency of executive problems of their children on a 3-point Likert scale. Raw scores on the global scale range from 63 to 189. The *t* scores (mean 50, SD 10) are used to evaluate the level of EF behaviors relative to normative samples. Higher scores indicate a worse outcome. As this questionnaire covers the age range of 5 to 18 years, scores of adolescents of 19 years have been standardized by considering norms for adolescents of 14 to 18 years.BRIEF 2–self-report form [64]: the BRIEF 2–self-report form questionnaire is aimed at assessing self-reported EF in everyday life of adolescents aged 11 to 18 years. It is composed of 55 items belonging to 7 clinical scales (ie, inhibit, self-monitor, shift, emotional control, task-monitor, working memory, and plan or organize) and 3 validity scales (ie, inconsistency, negativity, and infrequency). Raw scores on the global scale range from 55 to 165. The *t* scores (mean 50, SD 10) are used to interpret the level of EF compared to normative sample. Higher scores represent a worse outcome. As this questionnaire covers the age range 5 to 18 years, scores of adolescents of 19 years have been standardized by considering norms for adolescents of 14 to 18 years.Child Behavior Checklist 6 to 18 (CBCL 6-18) [65]: the CBCL 6 to 18 is aimed at assessing psychological adjustment and behavioral functioning of children and adolescents aged 6 to 18 years, as rated by parents. The questionnaire includes 113 items. The scores of this instrument considered for this study are total problems, internalizing problems, and externalizing problems. Raw scores of the Total Problems Scale range from 0 to 226 and are converted to *t* scores (mean 50, SD 10) to interpret the level of behavioral functioning compared to normative sample. Higher scores indicate a worse outcome. As this questionnaire covers the age range 6 to 18 years, scores of adolescents aged 19 years have been standardized by considering norms for adolescents aged 12 to 18 years.Youth Self-Report 11 to 18 (YSR 11-18) [65]: YSR 11 to 18 is aimed at assessing self-reported psychological adjustment and behavioral functioning of adolescents aged 11 to 18 years. The questionnaire includes 112 items. The scores of this instrument considered for this study are total problems, internalizing problems, and externalizing problems. Raw scores of the Total Problems Scale range from 0 to 224 and are converted to *t* scores (mean 50, SD 10) to interpret the level of behavioral functioning compared to normative sample. Higher scores represent a worse outcome. As this questionnaire covers the age range 11 to 18 years, scores of adolescents aged 19 years have been standardized by considering norms for adolescents aged 11 to 18 years.Beck Anxiety Inventory (BAI) [66]: the BAI is a 21-item questionnaire aimed at assessing state and trait anxiety in adults. In this study, the questionnaire is administered to parents to evaluate their psychological functioning. The total score is calculated as the sum of the 21 items (4-point Likert scale, ranging 0-3), with a minimum score of 0 and a maximum score of 108. Higher scores indicate a worse outcome. Specifically, a score of 0 to 21 indicates low levels of anxiety, a score of 22 to 35 indicates moderate levels of anxiety, and a score of 36 to 108 indicates potentially concerning levels of anxiety.Symptom Checklist 90 (SCL-90) [67]: the SCL-90 is a self-report questionnaire for adults aimed at measuring psychiatric symptom intensity on 9 different subscales (ie, somatization, obsessive-compulsive, interpersonal sensitivity, depression, anxiety, anger-hostility, phobic anxiety, paranoid ideation, and psychoticism). The 90 items included in the questionnaire are scored on a 5-point Likert scale (ranging 0-4), indicating the rate of occurrence of the symptoms during the last 7 days. In this study, the questionnaire is administered to parents to assess their psychological well-being. The Global Severity Index (GSI) is considered, for which the score is reported as a ratio of the sum of all items to the number of items scored. Higher scores indicate higher psychiatric symptom intensity; consistent with recommendations [65], an average score corresponding to ≥1 on the GSI enters the clinical range.Parenting Stress Index (PSI)–Short Form [68]: PSI–Short Form is a 36-item questionnaire aimed at assessing levels of stress associated with parenting in relation to different areas: parenting competence, restrictions on life introduced by parenting, parental conflict, depression, and social support. The 36 items of the questionnaire are scored on a 5-point Likert scale. The global score (PSI-total) is considered for this study, for which clinical cutoff is established at 90. Higher scores indicate higher distress.Jansari assessment of Executive Functions for Adolescents (JEF-A) [69]: JEF-A is a computerized assessment based on nonimmersive virtual reality aimed at evaluating everyday EF in adolescents aged 10 to 18 years. It is a performance-based assessment administered to adolescents. Participants are asked to plan, set up, and run a birthday party through the completion of 16 tasks resembling real-world activities. JEF-A tasks evaluate 8 constructs related to EF: planning, prioritization, selective thinking, creative thinking, adaptive thinking, action-based prospective memory, event-based prospective memory, and time-based prospective memory. All tasks are scored on a 3-point scale: 0 for failure, 1 for a partial or nonoptimal completion, and 2 for satisfactory completion. The scores for the 2 tasks for any particular construct are summed (ie, maximum of 4 possible), and this score is converted to a percentage of achievement for this construct. In addition to the 8 individual module scores, an average total percentage is computed for the whole assessment. The final raw score ranges from 0 to 32. Higher scores and percentages indicate a better EF. Although this instrument has been tested on adolescents with acquired brain injury (ABI) who are aged 10 to 18 years, in this study, we adopted it for participants aged 19 years as well to ensure comparability and a task in line with tasks related to such an age instead of administering to those adolescents the task for adults involving a multiple errand task based around a business office [70].A Developmental Neuropsychological Assessment-2 (NEPSY-2; Theory of Mind and Affect Recognition subscales) [71]: the Theory of Mind and Affect Recognition subscales of NEPSY-2 are performance-based subtests administered to adolescents and aimed at evaluating their social perception and emotion recognition skills. Theory of Mind subscale–part A measures understanding of mental functions and other people’s perspectives, and its raw scores range from 0 to 17; Theory of Mind subscale–part B examines the ability to match basic emotions (eg, happy, sad, angry, afraid, and disgusted) to specific situations, and its raw scores range from 0 to 8. The Affect Recognition subscale tests the ability to recognize emotions in facial expressions, and its raw scores range from 0 to 35. Raw scores are converted into scaled scores (mean 10, SD 3) based on age norms ranging from 1 to 19. Higher scores indicate better outcomes. As this battery covers the age range 3 to 16 years, scores of adolescents aged 17 to 19 years have been standardized by considering norms for adolescents aged 11 to 16 years.

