### Data Analysis Plan

All randomized adolescents will be included in the analyses, irrespective of adherence to treatment in the I-TOPS or wellness intervention. No imputation of a missing baseline or follow-up data will be performed. The *t* tests and chi-square analyses will be performed to compare the I-TOPS (ie, experimental) and wellness (ie, control) intervention groups on continuous and dichotomous variables, respectively. Similar analyses will be performed to examine baseline differences between patients who will complete the study and those who will drop out. Frequencies and means related to feasibility outcomes will be calculated. Analyses will be performed using SPSS (version 29.0.1.0; IBM Corp) [74].

Efficacy outcome measures will be separately entered into linear mixed effect models with “time” (baseline vs immediately after treatment vs 6-month follow-up) and “treatment” (regular I-TOPS vs wellness intervention) and their interaction as fixed factors and “intercepts” and “participants” as random factors. In case of differences in any clinical or demographic variables between groups at baseline, those measures will be included in the analyses as covariates. Mixed model analysis allows flexible modeling of the pattern of change over time and uses all the data for a given participant, even if that participant is not seen at all assessments, allowing us to retain participants with missing assessments. Significant interaction effects (ie, time and group) or group effects will be analyzed by post hoc tests. The significance threshold will be set at <.05. No interim analysis will be planned.

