### Conclusions

If this phase-2 RCT yields positive results, a larger, multicenter, phase-3 RCT could be planned and delivered to examine I-TOPS intervention efficacy and cost-effectiveness in a larger sample. Since 2020, Italy has a network for sharing the best practices related to rehabilitation for pediatric neurological children—Rete Pediatrica degli IRCCS [78]—with an important focus on telerehabilitation. This network could enroll in the phase-3 RCT, particularly given that the institute conducting the phase-2 RCT is part of this network.

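### Nine or more efficacy outcomes are each tested at .05 by two routes, with no primary efficacy outcome and no multiplicity control

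*Protocol article*

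**What the plan says.** The article (Efficacy Outcomes) announces: "A total of 9 outcome measures will be used to test preliminary evidence of training efficacy". The breakdown that follows, "7 self-assessed outcome measures (ie, 5 questionnaires for parents and 2 questionnaires for adolescents), 2 performance-based tasks assessing social cognition" plus a virtual reality assessment, adds to 7 + 2 + 1 = 10, because it counts the two NEPSY-2 subtests separately.

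Several instruments supply more than one score. For the CBCL, and in the same terms for the YSR: "The scores of this instrument considered for this study are total problems, internalizing problems, and externalizing problems". For the NEPSY-2: "the Theory of Mind and Affect Recognition subscales of NEPSY-2 are performance-based subtests administered to adolescents", with Theory of Mind further split into parts A and B.

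The testing rule is in the Data Analysis Plan: "Efficacy outcome measures will be separately entered into linear mixed effect models"; "Significant interaction effects (ie, time and group) or group effects will be analyzed by post hoc tests"; "The significance threshold will be set at <.05". Neither the Objectives nor the sections from Efficacy Outcomes to Data Analysis Plan name a primary efficacy outcome, a lead time point or an order of testing. The only outcome singled out is adherence, a feasibility measure (Sample Size and Power Calculation).

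The Conclusions of the Discussion add: "If this phase-2 RCT yields positive results, a larger, multicenter, phase-3 RCT could be planned". What would count as positive is not defined.

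**The concern.** Each outcome has two ways to reach significance, and there are many outcomes. Nothing in the stated rule limits the chance that an ineffective programme produces at least one significant efficacy result, and nothing says which result would carry the efficacy claim. Efficacy is the second stated objective, and the article uses significance tests to address it.

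The second route is also a weak efficacy test. The group main effect averages over all three assessments, including the pre-treatment baseline. It therefore dilutes any treatment effect and picks up chance baseline imbalance.

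The power statement rests on one test at .05, so a reader cannot tell which outcome the 80% refers to.

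**Working it through.** **1. Reproduce the stated sample size.** Inputs from Sample Size and Power Calculation: f = 0.2, correlation between repeated measures 0.50, α = .05, 2 groups, 3 time points, N = 42.

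- Within-between interaction, G*Power convention: λ = f²·N·m/(1−ρ) = 0.04 × 42 × 3 / 0.5 = 10.08, with df 2 and 80. Power is 80.3%. At N = 40 it is 78.2%, so 42 is the smallest even total that reaches 80%. The plan's figure reproduces.
- Group main effect, same inputs: λ = f²·N·m/(1+(m−1)ρ) = 0.04 × 42 × 3 / 2 = 2.52, with df 1 and 40. Power is 34%, and N = 134 would be needed for 80%.

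The stated N therefore belongs to one interaction test at .05.

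**2. Count the scores named in the description of outcome measures.** BRIEF-2 parent 1, BRIEF-2 self 1, CBCL 3, YSR 3, BAI 1, SCL-90 index 1, PSI total 1, JEF-A total 1, NEPSY-2 2 or 3. Total 14 or 15. The eight JEF-A construct scores are left out, because the article does not say they will be tested.

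**3. Independent outcomes, closed form: 1 − 0.95^k.**

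- Interaction only: k = 9 gives 37.0%; k = 14, 51.2%; k = 15, 53.7%.
- Either route (2k tests): k = 9 gives 1 − 0.95^18 = 60.3%; k = 14, 76.2%; k = 15, 78.5%.

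**4. Correlated outcomes, simulation.** No effect on any outcome, 21 per arm, three time points, within-person correlation 0.5, balanced random-intercept F tests, 16,000 runs per setting. The correlation r between outcomes is not in the article; 0 to 0.7 is an assumed range.

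| Chance of at least one p < .05 | r = 0 | 0.3 | 0.5 | 0.7 |
|---|---|---|---|---|
| 9 outcomes, either route | 60% | 55% | 48% | 38% |
| 9 outcomes, interaction only | 37% | 33% | 28% | 21% |
| 9 outcomes, either route, favouring I-TOPS | 37% | 31% | 27% | 21% |
| 15 scores, either route | 79% | 71% | 60% | 46% |
| 15 scores, interaction only | 54% | 46% | 37% | 27% |
| 15 scores, either route, favouring I-TOPS | 53% | 43% | 35% | 26% |

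Repeat runs moved individual entries by about one percentage point. A single outcome carries about 10% error through its two routes. The most lenient count, interaction only and favouring I-TOPS, gives 11–20% for nine outcomes and 14–32% for 15 scores.

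**5. Compare remedies at N = 42.** One named primary with one interaction test: 5% error, 80.3% power before attrition. Bonferroni over nine interaction tests (.05/9 = .0056): power per outcome 50.5%, and N = 68 needed for 80%.

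**The case against.** The strongest reply is that this is a single-centre phase-2 trial of 42 participants. Feasibility is its first objective, with criteria set in advance, and the article itself calls the efficacy evidence preliminary. A multiplicity rule is often left to a statistical analysis plan, which is not shown. This framing stands and lowers the consequence. It does not remove the point, because the article does state a rule (separate models, two routes, a flat .05), and the choice of lead outcome belongs with the sample size.

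A reader might infer that a falsely positive trial is about as likely as not. The article does not support that.

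- The highest figures count significant results in favour of the wellness arm.
- They also assume independence, which is implausible for overlapping scores such as CBCL total, internalizing and externalizing.
- The article says only that group effects will be followed up, not that they establish efficacy.
- The post hoc tests run only after a significant result, so they do not raise the error rate when nothing works.

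A reader might also take the phase-3 sentence as a decision rule that any one significant score would satisfy. The wording is that such a trial could be planned, which is an aspiration and not a go criterion.

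**Conclusion.** The point holds in this form: the published rule leaves the error rate across efficacy outcomes uncontrolled, and no outcome carries the efficacy claim or the power statement. Depending on how a false finding is counted, the chance of at least one runs from 11–20% (nine outcomes, interaction only, favouring I-TOPS) up to 46–79% (15 scores, either route, either direction), against a nominal 5%.

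The figures rest on no effect on any outcome, complete data with 21 per arm, the article's own within-person correlation of 0.5, and an assumed between-outcome correlation of 0 to 0.7. The count of 14 to 15 scores is read from the instrument descriptions; the article's own unit is nine measures. An unseen analysis plan could contain an adjustment, but the rule as published has none.

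**What to change.** In a dated addendum, before any between-arm outcome comparison:

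- Name one primary efficacy outcome that matches the executive-function aim. The choice is the sponsor's and should be justified.
- Test it at .05 with the time-by-treatment interaction used for the power calculation, and report the T1 and T2 contrasts as follow-up. A single T1 contrast as the primary test would depart from the test on which 42 participants rest.
- Do not treat the group main effect as evidence of efficacy.
- Apply Holm to the remaining outcomes, or report them as exploratory estimates with confidence intervals and no significance claims.
- Base any statement of positive efficacy results on the primary outcome.

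The cost is a short document and the loss of nominal significance claims for secondary outcomes. One caution concerns timing. The last evaluation was in February 2023, completion counts by arm are already published in the Abstract, and the supervising psychotherapists know the allocation. The addendum should therefore state who has seen arm-level outcome data; without that, the choice of primary cannot be shown to be free of the results.

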### Data Collection

Following completion of the consent process, sociodemographic information (eg, age, sex, and socioeconomic status); details of past medical history; concurrent medication; the adolescent’s age at the time of injury; and injury severity, measured using the Glasgow Coma Scale [61] will be collected from each patient’s referring physician. Family compositions will be collected from parents via telephone for outpatients or directly in the clinic for hospitalized patients who are close to discharge.

At baseline (T0), after treatment (T1), and at 6-month follow-up (T2), adolescents and parents will be asked to complete study outcome measures, including questionnaires on cognitive and behavioral functioning of adolescents, and the psychological well-being of parents and adolescents will undergo remote cognitive performance–based evaluations. Questionnaires will be sent to adolescents and families in a sealed envelope; after completing them, adolescents and parents will be required to return them to the research staff using an envelope with a postmark included in the sealed envelope within 2 weeks. To promote participant retention, support from a member of the research team could be given for questionnaire fulfillment, if needed. In addition, performance-based measures on adolescents’ cognitive functioning will be remotely administered, thus removing practical barriers to patient retention in the study, such as difficulties in transportation and reaching research centers.

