### Sample Size and Power Calculation

A previous meta-analysis on the effects of the original American TOPS program on the various outcomes found a small-to-medium average effect size (Hedges *g*=0.37) [37]; however, high variability was found among the effect sizes of the different studies analyzed. This led us, to be conservative, to estimate a small effect size of f=0.2 for the evaluation of the power calculation in the present study. Power analysis was conducted using G*Power3 Software (Heinrich-Heine-Universität Düsseldorf) [72,73]. Assuming a correlation of 0.50 between repeated measures and setting the α level at *P*<.05, a sample size of 21 participants per group will be required to obtain 80% of power with our 2 group- and 3 time-point- design. Therefore, a whole sample of 42 participants will be required to be included in the study. Attrition was not considered in performing power calculation, as adherence rates will be a core outcome of this study, which is pioneering for the Italian context and, therefore, will be aimed at collecting data on feasibility. Therefore, any eventual dropouts will be accounted for in statistical analyses using intention-to-treat analysis procedures.

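### Covariates are chosen by baseline differences between randomised arms, so chance rather than prognosis sets the efficacy model

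*Protocol article*

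**What the plan says.** The Data Analysis Plan in the protocol article states that t "tests and chi-square analyses will be performed to compare the I-TOPS (ie, experimental) and wellness (ie, control) intervention groups on continuous and dichotomous variables". The same section says "The significance threshold will be set at <.05", and then gives the covariate rule: "In case of differences in any clinical or demographic variables between groups at baseline, those measures will be included in the analyses as covariates". No covariate is named in advance.

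The pool of candidates comes from the Data Collection section: "sociodemographic information (eg, age, sex, and socioeconomic status); details of past medical history; concurrent medication", followed by age at injury, injury severity and family composition. That is about eight variables, and the list of sociodemographic items is given only as examples.

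The efficacy model has time (T0, T1, T2), treatment "and their interaction as fixed factors and “intercepts” and “participants” as random factors". Follow-up testing has two triggers: "Significant interaction effects (ie, time and group) or group effects will be analyzed by post hoc tests". The Randomization and Blinding section describes an unstratified coin-flip allocation made in a spreadsheet.

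**The concern.** The rule uses a test whose null hypothesis is already known to be true. Allocation is by an independent random draw, so a significant baseline difference in age or injury severity is a chance event. It says nothing about whether the variable predicts the outcome, which is the only reason to adjust for it.

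Three consequences follow. The model for each efficacy outcome cannot be written down before the data are seen. A strongly prognostic variable with a moderate imbalance stays out, while a variable of no prognostic value can be let in. And if a flagged variable enters simply as an additional main effect, it does little for the time-by-treatment interaction, the test for which the trial was sized.

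**Working it through.** **Inputs.** From Sample Size and Power Calculation: 21 per group, 42 in total, 3 time points, 80% power, alpha .05, "to estimate a small effect size of f=0.2" and "Assuming a correlation of 0.50 between repeated measures". From the abstract's Results: 34 of 42 assessed at T1 (19 and 15 by arm) and 31 at T2 (18 and 13). From Data Collection: about 8 candidate variables. Assumed: two-sided baseline tests, independent candidates, and the slopes and correlations given below.

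**1. The plan's own figure, and which test it belongs to.** For the repeated-measures within-between interaction, lambda = f² × N × m / (1 − rho) = 0.04 × 42 × 3 / 0.5 = 10.08, on 2 and 80 degrees of freedom. Power is 0.803, and 42 is the smallest even N that reaches 80%. The stated size reproduces. The between-group version of the same calculation gives only 0.34 at N = 42. The powered test is therefore the time-by-treatment interaction.

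**2. What the baseline test can flag.** The critical t on 40 degrees of freedom is 2.021, and the standard error of a standardised difference is √(2/21) = 0.3086. An observed gap must exceed 2.021 × 0.3086 = 0.62 SD to be flagged. Under randomisation an observed gap above 0.3 SD occurs with probability 0.337 per variable, and only 0.05 / 0.337 = 15% of those gaps are flagged. A gap above 0.5 SD occurs with probability 0.113, and 0.05 / 0.113 = 44% are flagged.

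**3. How often chance changes the model.** The probability that at least one of k independent variables is flagged is 1 − 0.95^k: 23% for k = 5, 34% for k = 8, 40% for k = 10.

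**4. Type I error for the group effect.** Take one covariate with correlation r to the outcome, no treatment effect, and an observed gap of 0.5 SD, which is below the trigger and so goes unadjusted. The expected group difference is 0.5r, with standard error √(1 − r²) × 0.3086. The unadjusted test rejects beyond about ±0.624.

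- r = 0.5: mean 0.25, standard error 0.267, z = (0.624 − 0.25) / 0.267 = 1.40, rejection about 8%.
- r = 0.7: mean 0.35, standard error 0.220, z = (0.624 − 0.35) / 0.220 = 1.24, rejection about 11%.

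Simulation of the two-stage rule agrees: 7% to 11% given a gap of 0.4 to 0.6 SD, against 5% when the covariate is always included. Averaged over all imbalances the rule rejects in about 4%. A separate simulation with 8 covariates, two of them prognostic, gave 0.049, 0.044, 0.041 and 0.035 for slopes 0, 0.3, 0.5 and 0.8. Overall error is nominal to slightly conservative.

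**5. Effect on the interaction.** Sixty random-intercept datasets were generated with 21 per arm, intraclass correlation 0.5, a covariate gap fixed at 0.7 SD, a covariate slope that rises by 0.3 after baseline, and no treatment effect. Mean estimated interactions:

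| Model | Complete data, T1 / T2 | Reported dropout, T1 / T2 |
|---|---|---|
| No covariate | 0.21 / 0.30 | 0.19 / 0.30 |
| Covariate as main effect | 0.21 / 0.30 | 0.19 / 0.30 |
| Covariate with time interaction | 0.01 / 0.09 | −0.01 / 0.07 |

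The main-effect term changed the interaction by less than 1e-14 with complete data. With the reported dropout it changed it by 0.04 on average and by at most 0.13. It moved the treatment coefficient by about 0.47 to 0.49. Only the covariate-by-time terms removed most of the spurious interaction.

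**The case against.** The strongest reply is that the article does not say some of what a critic might read into it. It says differences, not significant differences, and it does not say that covariates enter as main effects only. The functional form of a covariate is detail that a full plan may hold. This is also a phase-2 feasibility trial that seeks preliminary evidence of efficacy.

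Part of this stands. Main-effect entry is an inference from the fact that time by treatment is the only interaction listed, so the fifth step is conditional on it. Even then, exact invariance needs complete data, which this trial does not have. The plan also follows up group effects, and a main-effect covariate does adjust those.

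Two stronger readings should be set aside. A reader might infer that the rule inflates false positives; applied mechanically, it does not, and the overall rate is at or just below 5%. A reader might also infer that the test misses imbalance of every size. In fact every observed gap above about 0.62 SD is flagged; it is the smaller gaps that go through.

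What does not stand is the idea that this is detail left to another document. The trigger is a stated rule. If differences means something other than the tests named beside it, the rule is undefined and still driven by the data.

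**Conclusion.** The concern holds in a limited form. Covariates are selected by chance differences between randomised arms, so the efficacy model is not fixed in advance and is not chosen for prognosis. At 21 per arm, observed gaps up to about 0.62 SD go unadjusted, and about 34% of trials would flag at least one of 8 variables by chance alone.

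The harm is lost precision, and error that departs from 5% once the imbalance is known: roughly 7% to 11% at gaps of 0.4 to 0.6 SD with outcome correlations of 0.5 to 0.7. It falls mainly on the group effect. Under main-effect entry the rule gives the time-by-treatment interaction almost no protection.

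These sizes rest on equal arms of 21, independent candidate variables, two-sided tests, and the assumed slopes and correlations. The sample size itself is not in dispute. The change should be made, because the article's Results section places the analysis after publication of the protocol, but the point does not undermine the trial.

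**What to change.** - Delete the trigger sentence and the between-arm baseline significance tests. Report baseline characteristics descriptively by arm, for example with standardised differences.
- Before analysis, fix one or two prognostic variables already collected, for example age together with injury severity or age at injury. Use them for every outcome whatever their baseline difference. The article does not show which variables are prognostic, so give the reason for the choice.
- Enter each covariate with its time interaction, so that it adjusts the T1 and T2 contrasts as well as the group effect.
- Handle the T0 outcome once. Either keep T0 among the responses in a constrained-baseline model (a common T0 mean for both arms), or use T0 as a covariate and remove it from the responses. Doing both would put baseline on both sides of the model.

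The cost is wording, plus about three parameters per continuous covariate when T0 stays among the responses: one main effect and two time interactions. Two covariates then use 2 × 3 = 6 parameters. With 42 participants and 31 seen at T2 that is not trivial, which is why the list should stop at one or two.
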